### Trial oversight

We will constitute a trial managing group (TMG) consisting of PIs/co-PIs and trial managers from all the sites, the trial statistician and representatives from the sponsor. The TMG will meet at prespecified intervals for reviewing and coordinating the conduct of the trial at the site level. The TSC will also be formed for the trial governance. The TSC will have members from the TMG (PIs and trial statistician), independent members and Patient and Public Involvement (PPI) representative. The main role of TSC will be to provide overall supervision for the trial and give advice through its independent chair on trial-related matters. The final decision regarding the continuation of the trial will rest with the TSC. The TSC will also oversee the dissemination of the results of the trial and the publication process.

### Recruitment strategies

All the sites are large tertiary care centres with a high volume of clinical work and eligible population. We do not anticipate any difficulty in recruitment. However, we will monitor the recruitment rate per site every 6 months. During the monthly TMG meetings, those sites with slower accrual (less than five participants per site per month) will be advised to identify the reasons for the lower recruitment rate and take the necessary corrective steps. Furthermore, we have a review plan to review site performance after 1 year and in case of any slow accrual from any site, we will allocate additional participants to other performing sites.

### Patient and public involvement

Members from the public as well the patients will be invited, and a group will be formed which will help at the design stage as well as be involved in trial governance through TSC.

### Ancillary study

The ancillary study has not been planned for the current project. However, the individual sites can explore translational research at individual sites after seeking permission from TSC as well as seek fresh ethics committee approval and separate funding for the same.

Additional blood samples will be stored for possible future translational research. Written informed consent incorporates the same and the participants will be informed about the future study.

### Sample size calculation

No previous data is available on live birth following individualized lifestyle intervention in PCOS women who wish to conceive. From previous study performed in one of the trial sites, the live birth rate following usual care which consisted of one-time lifestyle advise and ovulation induction with Letrozole for up to five treatment cycles, was reported as 30% [25]. Due to uncertainty about the likely event rate (live birth rate) in the intervention arm, it was assumed that to convince the clinicians and patients to adopt a change in practice, a modest improvement of 10% in live birth would be required.

For alpha error set at 0.05 and power being 90%, to detect a clinically relevant difference of 10% in the live birth rate following individualized lifestyle intervention, the calculated sample size will be 473 in each arm (total sample size 946). Assuming an attrition of 20%, the total sample size was 1183. We rounded off the total sample size to 1200 with 600 in each arm. With 5 centres participating in the study each site shall recruit 240 subjects each.

### Statical analysis

Data will be entered using ICMR software (developed by ICMR, New Delhi) and screened for outliers and extreme values using Box-Cox plot and histogram (for the shape of the distribution). Summary statistics will be used for reporting demographic and clinical characteristics using mean (SD)/median (range) for the continuous variables, and frequency along with percentage for categorical variables. An intention-to-treat analysis and per-protocol analysis for the primary and secondary endpoints will be performed. The continuous endpoints will be tested using *z*-test for means, and the difference in means will be presented with 95% CI. The categorical endpoints will be tested using *z*-test for proportions and the difference in proportion will be presented with 95% CI. A generalized estimating equations (GEE) will be performed to understand the compliance and the effect over time between the two groups of intervention. To understand the advantage of intervention the number needed to treat will be presented.

Based on BMI 23–27 and > 27–35 kg/m^2^, we will perform subgroup analysis to explore whether there is any difference in the effect of the intervention in different subpopulations.

All the randomized subjects will be included in the intention to-treat (ITT) analysis. The ITT analysis is done for the primary endpoint and secondary endpoints and analysed according to the group assigned by randomization. For dropouts with no information on the outcome, it will be assumed that the intervention did not result in a live birth (Table 1).

Per-protocol set (PPS) is the subset of ITT, where the subjects are randomized and treated without any major protocol deviations that impacts the efficacy of the results. The PSS will be used for primary endpoint analysis and secondary end-points. The analysis set will be the subset of participants who are not dropped out of the study and satisfy the protocol requirement. Non-compliant will not be considered for the per-protocol analysis but will be included in the ITT (Table 1). We will perform additional analysis for partially compliant participants and include them in the per-protocol analysis (Table 1). The analysis will be performed by creating an interaction term for the intervention group with partially and fully complaint groups presenting multiple testing-adjusted *p*-values.

We plan to adjust the results for the following covariates: (i) number of letrozole cycles. Logistic regression analysis will be used to adjust the covariates effectively the adjusted effect size will be presented as an odds ratio (95% CI) for binary outcomes. All the analyses will be performed using STATA/IC 16.0.

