### Sequence generation and allocation concealment

Once eligibility is confirmed, web-based randomization will be initiated in the presence of the trial staff. The randomization will be done using PHP as the frontend and MySQL as the backend database. Block randomization stratified for the site and BMI (≥ 23–27 kg/m^2^ and > 27 to ≤ 35 kg/m^2^) will be performed. The randomization will be done in a 1:1 ratio to the intervention or the control arm. The trial staff from each site will enter the participant information following which a randomization number will generated and assigned if they fulfil the eligibility criteria. The random number and the allotted arm details will be provided to the trial staff by an authorized person in each site. The allocation will be concealed until the point of randomization. The allotted intervention will be informed to the clinical team as well as the trial staff, and the trial number will be noted.

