### Secondary outcomes

There will be several secondary outcomes which will measure clinical, endocrinological and quality of life parameters and are listed below:(i)Clinical pregnancy rate (time frame: 0 to 9 months post-randomization for participants who conceive within 6 months following randomization): ultrasound evidence of gestational sac or definitive clinical evidence of pregnancy. An ectopic pregnancy will also be considered a clinical pregnancy [24].(ii)Ongoing pregnancy rate (time frame: 0 to 9 months post-randomization for participants who conceive within 6 months following randomization): a viable intrauterine pregnancy as documented by ultrasound after 12 completed weeks of gestation.(iii)Miscarriage rate (time frame: 0 to 12 months post-randomization for participants who conceive within 6 months following randomization): miscarriage is defined as a spontaneous loss of pregnancy before 20 completed weeks of gestational age [23].(iv)Ectopic pregnancy rate (time frame: 0 to 9 months post-randomization for participants who conceive within 6 months following randomization): ectopic pregnancy is defined as pregnancy outside the uterus as diagnosed by ultrasound, surgically or by histopathology [24].(v)Stillbirth: defined as the death of a foetus prior to the complete expulsion or extraction from its mother after 20 completed weeks of gestational age [23].(vi)Time to pregnancy (time frame: 0 to 8 months post-randomization for participants who conceive within 6 months following randomization): from randomization to the documentation of pregnancy (calculated in days).(vii)Positive pregnancy rate (time frame: 0 to 7 months for participants who conceive within 6 months following randomization): defined as positive urine pregnancy test or serum beta human chorionic gonadotrophin (hCG) > 5 IU/ml.(viii)Mean weight loss (time frame: 6 months post-randomization): difference between baseline and follow-up at 6 months).(ix)Improvement in menstrual regularity (time frame: 6 months post-randomization): (according to the International Federation of Gynecology and Obstetrics (FIGO) 2018 guidelines variation of the cycle to be called regular is 7–9 days depending on age. Age 18–25 years ≤ 9 days; age 26–41 years ≤ 7 days is regular); proportion of women in whom regularization of the menstrual cycle is recorded by a total number of women in whom menstrual regularity is recorded.(x)Differences in anthropometric parameters (time frame: 6 months post-randomization) (waist circumference, hip circumference, neck circumference, waist hip ratio, waist height ratio and wrist circumference) at the end of the trial period.(xi)Improvement in hormonal and metabolic parameters (time frame: 6 months post-randomization) [biochemical markers such as lipid profile and glycaemic parameters, visceral adiposity index (VAI) and lipid accumulation product (LAP)] over the baseline.(xii)Quality of life (PCOS specific) assessment (time frame: 6 months post-randomization) [22].(xiii)Pregnancy-related complications (time frame: 0–17 months post-randomization for participants who conceive within 6 months following randomization) (GDM, PIH, preterm birth): obstetric outcomes—gestational diabetes, hypertensive disorder of pregnancy, preterm delivery (< 37 weeks), very preterm birth (< 32 weeks), low birth weight (< 2500 g) or high birth weight (> 4000 g)

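### The main comparisons ignore the site and BMI strata used in randomisation, and continuous outcomes are not adjusted for baseline: the tests stay valid, but precision is given away

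*Protocol article*

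**What the plan says.** The section on sequence generation specifies "Block randomization stratified for the site and BMI", with two BMI bands (23 to 27, and above 27 to 35 kg/m²). Study setting lists five sites, so there are ten strata.

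The Statical analysis section then names the tests. For categorical endpoints, which include live birth, it is a z "test for proportions and the difference in proportion will be presented with 95% CI". For continuous endpoints it is a z "test for means, and the difference in means will be presented with 95% CI". Neither carries a stratum or baseline term. The section also plans:

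- a GEE on compliance and on the effect over time, with no covariates listed;
- a subgroup analysis by BMI band;
- a logistic regression whose covariate list has a single entry, the number of letrozole cycles.

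Site is not mentioned in the analysis section.

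Baseline hormonal, metabolic, anthropometric and quality-of-life values are collected at session 1 (weeks 0 and 1). Among the secondary outcomes, weight (viii) is a baseline-to-6-month difference and the hormonal and metabolic outcomes (xi) are improvements over baseline. Item (x) reads "Differences in anthropometric parameters (time frame: 6 months post-randomization" and refers to the end of the trial period.

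**The concern.** Blocking within strata balances the arms on site and BMI band, so differences between strata no longer contribute to chance variation in the arm comparison. An unstratified z-test still counts that variation in its standard error. The reported error is then larger than the true one, and the balance obtained by stratifying is not turned into precision.

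Differences between sites are plausible here. The sites lie in different regions of India, the control arm is treated according to unit protocol, and the number of letrozole cycles (up to three) depends on unit policy. BMI band was considered important enough to be both a stratifier and a subgroup factor.

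For continuous outcomes the issue is similar. A baseline value that correlates with the 6-month value explains part of its variance, and a z-test on raw change or on the final value uses that information incompletely or not at all.

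The planned logistic regression does not close the gap. Its one covariate is neither a stratum nor a baseline value. Whether adjusting for letrozole cycles is appropriate is a separate question and adds no weight to this one.

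**Working it through.** **The plan's own figure.** The Sample size calculation section takes 30% in controls and aims "to detect a clinically relevant difference of 10% in the live birth rate following individualized lifestyle intervention", with alpha 0.05 and power 90%. Taking the test as two-sided and the variance as unpooled:

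n = (0.30×0.70 + 0.40×0.60) × (1.960 + 1.282)² / 0.10² = 472.8, rounded up to 473 per arm.

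This matches "the calculated sample size will be 473 in each arm (total sample size 946". Attrition: 946/0.80 = 1182.5, rounded up to the stated 1183. The sample size arithmetic is not at fault.

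**Primary endpoint: variance.** The documents give no live-birth rates by site or BMI band, so two sets of control rates are assumed for five equal sites, each averaging 30%. The ratio of within-site to unstratified variance is mean[p(1−p)] / [0.30×0.70].

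| Assumed site rates | mean p(1−p) | Ratio to 0.21 | Unstratified variance too large by | Standard error too large by |
|---|---|---|---|---|
| 20, 25, 30, 35, 40% | 0.205 | 0.976 | 2.4% | 1.2% |
| 15, 20, 30, 40, 45% | 0.197 | 0.938 | 6.6% | 3.2% |

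Under the null, the z-test's effective critical value is 1.96/√ratio, which is 1.984 and 2.024. The true type I error is therefore about 0.047 and 0.043, against a nominal 0.050.

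**Primary endpoint: power.** Take 473 per arm and add 10 points to every site's rate in the intervention arm. The true standard error is √[(mean p(1−p) control + mean p(1−p) treated)/473]. The unstratified test uses a null standard error of √(2×0.35×0.65/473) = 0.03102. The stratified test uses the within-site pooled version. Power is Φ[(0.10 − 1.96 × null SE)/true SE].

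- Rates 20-40%: true SE √[(0.205+0.235)/473] = 0.03050; stratified null SE √(2×0.2225/473) = 0.03067. Power is 0.901 unstratified and 0.905 stratified, a difference of 0.4 points.
- Rates 15-45%: true SE √[(0.197+0.227)/473] = 0.02994; stratified null SE √(2×0.2145/473) = 0.03012. Power is 0.905 unstratified and 0.914 stratified, a difference of about 1.0 point (0.96).

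**Simulation check.** Ten equal strata, 47 per arm per stratum, 200,000 trials per scenario, overall rates 30% and 40%, z-test against Cochran-Mantel-Haenszel (CMH):

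| Assumed stratum control rates | Type I error, z / CMH | Power, z / CMH |
|---|---|---|
| no stratum effect | 0.050 / 0.050 | 0.897 / 0.897 |
| 20-41% | 0.049 / 0.050 | 0.900 / 0.902 |
| 15-48% | 0.044 / 0.049 | 0.904 / 0.911 |
| 11-56% | 0.040 / 0.050 | 0.908 / 0.922 |
| 7-64% | 0.034 / 0.050 | 0.916 / 0.938 |

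**Continuous outcomes.** Let r be the baseline to 6-month correlation, which is assumed, with equal variances at both times. Relative variances are 1 for the final value, 2(1−r) for change, and 1−r² for ANCOVA.

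| r | Final value | Change | ANCOVA | ANCOVA saving vs change | ANCOVA saving vs final value |
|---|---|---|---|---|---|
| 0.5 | 1 | 1.00 | 0.75 | 25% | 25% |
| 0.8 | 1 | 0.40 | 0.36 | 10% | 64% |

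**The case against.** The strongest defence is that nothing here is invalid. The z-test never exceeds its nominal error rate in these scenarios, the likely loss on live birth is a fraction of a point of power up to about one point, and the stratum rates behind even that are assumed. Losses above one point, up to 2.2, need stratum rates as wide as 11-56% or 7-64%. All of this stands.

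It can also be said that an article leaves model detail to an SAP. That holds for the GEE, whose covariates are simply not given. It does not hold for the main comparisons, where the article names the tests and lists the covariates, and what it names does not match the randomisation.

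Several stronger readings are tempting but unsupported:

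- **Inflated false positives.** A reader might infer that ignoring the strata raises the type I error. The direction is the opposite: intervals are slightly too wide.
- **Baseline ignored throughout.** Weight and the hormonal and metabolic outcomes are defined as change from baseline. What is missing there is adjustment for the baseline value.
- **A 64% gain across the board.** That figure applies only to a final-value comparison at r = 0.8. A saving of more than half needs r above about 0.71 (1−r² < 0.5).
- **Nothing but z-tests.** A GEE and a logistic regression are also planned, although neither is stated to include the strata.
- **Sites choosing between timed intercourse and IUI by policy.** The medical treatment section ties that choice to the participant's profile; only the number of cycles is left to unit policy.

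Two practical limits on the remedy also stand. AMH and SGPT are listed at week 26 but not at session 1, so they have no listed baseline. Session 1 follows randomisation on the same day in an open-label trial, so a self-reported quality-of-life score taken once the arm is known is a less clean covariate than weight or a laboratory value.

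**Conclusion.** The point holds as one of efficiency. The analysis does not use the factors by which the trial is randomised, and baseline values that are collected do not enter as covariates. For live birth the cost is small and in the safe direction: a variance about 2-7% too large and under about one point of power for assumed site rates of 20-40% to 15-45%, more only with stronger stratum effects. For continuous secondary outcomes the cost can be larger: 10-25% of variance against change scores, and 25-64% against a final-value comparison, for assumed correlations of 0.8 and 0.5. The final-value figures matter only if item (x) is read that way. Neither the site rates nor the correlations are in the documents. The mismatch itself rests on the text and not on these assumptions.

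**What to change.** Primary analysis: report the risk difference for live birth with its 95% CI, stratified by site and BMI band. Either a Mantel-Haenszel estimate or a standardised risk difference from logistic regression on arm, site and BMI band would serve. Derive the number needed to treat from that estimate, and treat other binary outcomes in the same way.

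Continuous outcomes: use ANCOVA on the 6-month value with arm, the baseline value of the same measure, site and BMI band. Where no baseline is listed (AMH, SGPT), adjust for site and BMI band only. State for item (x) that the 6-month value is analysed with its baseline as covariate, which removes the ambiguity between final value and change. For quality of life, state whether the session 1 score is taken before the participant learns her allocation.

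The cost is wording, settled before outcome data are examined. The strata are recorded at randomisation and the listed baselines are already collected, so no added visit, test or participant is needed, and the planned 473 per arm stays sufficient.

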**Control arm**		
At 6 months	Point of assessment 3	Point of assessment 4
Ovulation induction with letrozole	Yes	Yes

For per protocol analysis inclusion only

• Compliance: for a minimum of three points of assessment and at least one ovulation induction cycle with letrozole (intervention arm)

• Compliance: for both the time points (3 and 4) and at least one ovulation induction cycle with letrozole (for control)

Additional analysis (partial compliance)

• Compliance for at least 2 time points of assessment in the intervention (per protocol will include full compliance and those who were partially compliant) and at least one cycle of ovulation induction

• Compliance at least in 1 time point plus at least one cycle of ovulation induction in the control arm

The following will be included in the intention-to-treat analysis only (not included in per protocol or additional analysis)

• Compliance for less than 2 time points irrespective of ovulation induction for intervention

• Compliance for no time points irrespective of ovulation induction for control

• Did not take ovulation induction irrespective of compliance for both the arms

• Who were dropouts (did not turn up at 6 months)

• Did not receive intervention for at least 4 months

Criteria for deciding non-compliance at each visit:

• Diet: participant consuming > 100 cal over the recommended calories intake

• Exercise: participant GPAQ score < 600

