## Discussion

Lifestyle intervention is considered as the first line of management for treating PCOS women who present with infertility. While earlier studies have shown some improvement in menstrual symptoms, endocrinological parameters and ovulation rate, very few have reported clinically important fertility outcomes, i.e. live birth [11–14]. The current trial is planned to capture all the relevant clinical domains which are important to the PCOS women such as reproductive outcomes, improvement in menstrual symptoms, changes in anthropometric measurements and endocrinological parameters and, finally, the quality-of-life score.

High dropout rates and adherence issues are some of the challenges in trials evaluating lifestyle intervention [10, 26]. The Cochrane review evaluating the lifestyle intervention reported high dropout rates (up to 46%), especially in studies involving longer treatment periods [10]. A systematic review investigated the dropout rates in studies evaluating the lifestyle intervention in overweight and obese infertile women [26]. The review included 15 studies, out of which 10 reported the dropout rate. The median dropout rate was 24% (range 0–31%). The authors could not find any modifiable predictors for dropouts and reported lower weight loss in women who had dropped out of the trial. The current study has calculated the sample size taking into account the possibility of high attrition (20%) that may be encountered during the conduct of the trial. In the currently planned trial, it has been hypothesized that customized lifestyle intervention delivered by the medical staff other than the treating clinician may help in greater adherence and lower dropouts. The study will indirectly help us investigate the impact of such an approach on the attrition rate for the lifestyle intervention.

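### The continuous secondary endpoints are planned as ITT on all randomised women, but the stated test and the only dropout rule make them available-case comparisons that can be biased in either direction

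*Protocol article*

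**What the plan says.** All of this is in the protocol article.

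- **Population.** *Statical analysis* includes every randomised woman in the ITT analysis and adds: "The ITT analysis is done for the primary endpoint and secondary endpoints".
- **Test.** The same section compares continuous endpoints by a z-test for means, with a difference and 95% CI.
- **Dropout rule.** The only one is: "For dropouts with no information on the outcome, it will be assumed that the intervention did not result in a live birth". It covers live birth and no other endpoint.
- **Outcomes.** Under *Secondary outcomes*, weight loss (viii), anthropometry (x), hormonal and metabolic parameters (xi) and quality of life (xii) all have a 6-month time frame.
- **Who is a dropout.** Table 1 lists, among women kept for ITT only: "Who were dropouts (did not turn up at 6 months". *Dropout criteria* words it differently, naming the visits at both 3 and 6 months and adding withdrawal of consent.
- **Contact by arm.** The schedule gives the intervention arm weekly messages, monthly calls and a week-13 visit with a weight check. The control arm has no planned compliance follow-up before 6 months.
- **What is known about dropouts.** The Discussion describes a systematic review with a median dropout of 24% (range 0–31%) that "reported lower weight loss in women who had dropped out of the trial". Another review it cites found dropout of up to 46%.

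**The concern.** Three commitments in one section do not fit together for outcomes (viii) and (x)–(xii): all randomised women, a two-sample z-test, and a dropout rule for live birth only. A woman who does not attend at 6 months has no value to enter. If the plan is followed as written she falls out of the test, while the result is still called ITT.

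Weight loss is central to the rationale in the Background, so readers will look to this comparison to explain whatever is found for live birth. The protocol itself reports that dropouts in earlier studies lost less weight, and it gives the two arms very different amounts of contact. A comparison restricted to women who stayed may therefore differ from the effect of assignment.

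**Working it through.** **1. The plan's own figures.** With 30% against 40%, power 90% and two-sided alpha 0.05 (sidedness is not stated, but two-sided reproduces the result), the unpooled normal formula gives

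(1.960 + 1.282)² × (0.30×0.70 + 0.40×0.60) / 0.10² = 473 per arm, or 946 in total.

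Inflation for attrition gives 946 / 0.80 = 1183, rounded in the plan to 1200. Both figures reproduce, so the sample size is not in question.

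**2. How many women leave the z-test.** At 20% attrition, 0.20 × 1200 = 240 women have no 6-month value. That leaves 960, or 480 per arm if loss is equal. At the cited median of 24% it would be 0.24 × 1200 = 288.

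The two wordings of dropout do not alter this. A woman who attends at 3 months but not at 6 is a dropout under Table 1 and arguably not under *Dropout criteria*, yet her 6-month value is missing either way.

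**3. Bias of the available-case difference.** For each arm (I, intervention; C, control) let m be the mean weight loss in completers, d the dropout share, and k the completers' mean loss minus the dropouts' mean loss.

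- Available-case difference: mI − mC
- All-randomised difference: (mI − dI·kI) − (mC − dC·kC)
- Bias: dI·kI − dC·kC

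The protocol gives no k and no dropout by arm, so the values below are assumptions that show the range.

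| dI | dC | kI (kg) | kC (kg) | Bias (kg) |
|---|---|---|---|---|
| 20% | 20% | 2 | 2 | 0.0 |
| 20% | 20% | 2 | 0 | +0.4 |
| 30% | 10% | 2 | 2 | +0.4 |
| 30% | 10% | 3 | 1 | +0.8 |
| 10% | 30% | 2 | 2 | −0.4 |
| 10% | 30% | 0 | 2 | −0.6 |

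As a gauge, with an assumed SD of 4 to 6 kg and 480 per arm, the standard error is SD × √(2/480) = 0.26 to 0.39 kg. A shift of 0.4 kg is then about 1.0 to 1.5 standard errors.

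**4. Where a 25% overstatement comes from.** Suppose assignment has no effect in dropouts and dropout is d in both arms. Then kI − kC equals the completer difference Δ, the all-randomised difference is (1 − d)Δ, and the ratio is 1/(1 − d). This gives 1.25 at 20%, 1.32 at 24% and 1.45 at 31%. Both assumptions are needed.

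**5. What each remedy does.** Assume completers lose 4 kg and 2 kg (Δ = 2.0) and dropouts lose nothing.

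- *Dropouts set to baseline*, (1 − dI)×4 − (1 − dC)×2: 1.6 kg at 20%/20%, 1.0 kg at 30%/10%, and 0.9×4 − 0.7×2 = 2.2 kg at 10%/30%.
- *Multiple imputation by arm from baseline variables only:* if dropouts and completers are alike at baseline, the imputed mean in each arm is in expectation the completers' mean. The estimate is (1 − d)m + d·m = m per arm, and the difference stays at 2.0 kg. Dropouts have been given the completers' effect.

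**The case against.** The strongest reply is that this is an omission. Handling of missing secondary data is commonly left to an SAP, the document is a condensed article, and an available-case comparison by assigned arm is often called ITT. The definition of menstrual regularity (ix) already restricts its denominator to women with a recorded status, which suggests that such analyses were intended. It stands that the lack of an imputation method is not in itself a finding. What remains is that the article does not defer: it fixes a population, a test and a dropout rule that cannot all hold for (viii) and (x)–(xii).

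A reader might infer that the plan will overstate the weight effect, by 25% to 45%. The documents do not support that. The finding on dropouts in the Discussion is not split by arm, and equal dropout with an equal shortfall gives no bias. The Discussion also hopes that customised delivery will lower dropout. If that leaves more loss in the control arm, among women who lose little weight, the effect is understated. The percentages need a zero effect in dropouts and equal dropout by arm, and the protocol states neither.

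The planned GEE might seem to answer the point. It is intended for compliance and effect over time, not named as the ITT test. Standard GEE generally needs missingness unrelated to outcome, and controls have no scheduled weight between baseline and 6 months.

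One limit also stands. Women who conceive stop the trial's lifestyle advice, and their 6-month weight may reflect pregnancy. Neither the plan's test nor the change proposed here deals with that.

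**Conclusion.** The point holds as an internal conflict affecting secondary outcomes (viii) and (x)–(xii). At the planned 20% attrition about 240 of 1200 women would be absent from tests said to include everyone.

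Bias is plausible because dropouts in the cited review lost less weight and contact differs by arm, but its sign is open. Over the assumed scenarios it runs from about −0.6 to +0.8 kg and passes through zero. The overstatement factor of 1/(1 − d) is one conditional case and not a forecast.

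The primary endpoint has its own dropout rule and is unaffected, as is the sample size. This should be corrected before outcome data are seen, but it does not threaten the trial's main conclusion.

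**What to change.** In *Statical analysis*, for outcomes (viii) and (x)–(xii):

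1. Replace the z-test for means by a linear regression of the 6-month value on arm, adjusted for baseline value, site and BMI stratum. In large samples this will usually be more precise than the z-test. It corrects for selective dropout only as far as those covariates explain it.
2. Call this observed-data comparison an available-case analysis, and report dropout by arm.
3. Prespecify a sensitivity analysis that departs from missing at random: either dropouts in both arms set to their baseline value, or delta-adjusted multiple imputation over a stated range by arm.
4. Do not present multiple imputation by arm from baseline variables alone as removing the bias.
5. Do not carry forward the week-13 weight, which is scheduled in the intervention arm only.
6. Reconcile the dropout definition in *Dropout criteria* with the one in Table 1.

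The cost is analysis text and some programming, with no new data. The sensitivity result may be less favourable to the intervention than the available-case result, although with heavier control loss it could move the other way.
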